### Confidentiality and access to data

All the data collected as part of the study will be kept strictly confidential and in accordance with the General Data Protection Regulation (GDPR). Participants are provided with detailed information relating to confidentiality in the participant Information Sheet. Northumberland Tyne and Wear NHS Foundation Trust (NTW) is the sponsor and will act as the data controller. The study is being led and managed by Newcastle University, who are acting as a data processor. NTW and Newcastle University will keep identifiable information about participants until 3 years after the youngest child in the study reaches 18 years old. The local study team at NTW and Newcastle University will use participants’ names and contact details to contact them about the research study, and make sure that relevant information about the study is recorded for their child’s care, and to oversee the quality of the study. Individuals from NTW, Newcastle University, and regulatory organisations may look at the research records to check the accuracy of the research study. The only people who will have access to information that identifies participants will be people who need to contact them about the study or audit the data collection process. All information will be stored in a secure and locked office, and on a password-protected database. Any information which leaves the hospital or university sites will have names and addresses removed (anonymised) and a unique code will be used. Personal data (name, address, email, telephone number) will be kept after the end of the study so that we are able to contact participants about the findings of the study.

### Randomisation and blinding

Participants are randomised on a 1:1 basis to receive either CUES or Understanding Autism, without stratification. Randomisation occurs online through Sealed Envelope (https://www.sealedenvelope.com/). Participants will be aware of group status due to the nature of the intervention, but the primary outcome assessor will be blind to group allocation although, despite instruction not to do so, participants could unwittingly break blindness if they reveal details about the intervention at post-treatment assessment.

### Procedure

The researcher will meet with the participant at home to explain the study, answer questions, obtain informed consent (and assent from the child), and undertake the baseline characterisation and target uncertain situation interviews. This may be split into two visits depending on logistics (e.g., parents’ availability) and the length of time the interviews take, as this will vary between participants. Prior to the first visit, the assessments in questionnaire format are posted to the parent to complete. These are collected once the participants have been consented at the home visit(s).

### Primary and secondary outcomes

We are aiming to determine whether CUES is feasible to deliver through NHS services by trained therapists, and if it is acceptable and well received by families. Also, we will investigate whether successfully targeting IU will result in an increased tolerance to uncertainty and a downstream reduction in a range of anxiety disorder symptoms, alongside an increase in children’s social participation as evidenced by the respective outcome measures. In addition, we will explore whether participation in CUES will have a beneficial effect on parental wellbeing.

#### Baseline characterisation

The characteristics and functional abilities of the child with ASD will be measured by the Social Communication Questionnaire (SCQ; [36]) (parent reporting on child). This is a 40-item questionnaire which is used internationally and has high sensitivity and specificity for an ASD diagnosis [36]. We will also use the Vineland Adaptive Behaviour Scales III (VABS III; [37]) (parent reporting on child). The number of items depends on the child’s developmental level. It has demonstrated excellent internal consistency (α = 0.90 to 0.98) and content, construct, and concurrent validity [37].The anxiety characteristics of the child with ASD will be measured with the Anxiety Disorders Interview Schedule — Autism Spectrum Addendum (ADIS-ASA; [38]) (parent reporting on child). The number of items depends on the child’s symptoms of anxiety. It is a reliable measurement of comorbidity (intraclass correlation (ICC) = 0.85–0.98; κ =0.67–0.91) as well as ambiguous anxiety-like symptoms (ICC = 0.87–95, κ = 0.77–0.90) in children with ASD. Convergent and discriminant validity were supported for the traditional anxiety symptoms on the ADIS/ASA, whereas convergent and discriminant validity were partially supported for the ambiguous anxiety-like symptoms. We will all interview the parent to obtain information about the child’s current treatment and other health service usage; concurrent life events that may influence mood; perceived impact of anxiety on the child’s education and participation in everyday events; and impact of the child’s anxiety on other members of the family (parent reporting on child).

#### Feasibility and acceptability outcomes

The outcomes are acceptability of all aspects of the trial (including outcome measures, acceptability of intervention materials and methods, use of strategies outside of sessions, and any perceived benefits after treatment) and feasibility (including experience of recruitment, randomisation, and visits to the home). These will be obtained via parent interview (parent self-report and parent reporting on child) and the Credibility and Expectancy Questionnaire [39] (parent self-report). The CUES group completes a 10-item questionnaire and the Understanding Autism group completes a 6-item questionnaire. This has demonstrated high internal consistency within each factor (α = 0.86) and good test–retest reliability. The expectancy factor predicts outcome on some measures, whereas the credibility factor is unrelated to outcome [39]. We will also conduct interviews with therapists.

#### Main research outcome

The main research outcome is to target uncertain situations that cause the child to experience anxiety due to IU (parent reporting on child) using a target behaviour rating. Parents will be asked to identify two target real-life situations that might cause their child significant IU (method validated in our pilot work [5]), one situation that their child would like to do but currently cannot do or not do consistently (e.g. playing with friends in the neighbourhood), and one situation that is appropriate and necessary for them to do due to normal developmentally appropriate educational, social participation, or inclusion outcomes (e.g. attending swimming lessons). Through a semistructured interview, parents will be asked what about the situation is uncertain, how often it occurs, the child’s reaction (symptoms and intensity), whether the child worries about the situation in advance, and how it interferes with daily functions and activities for the child and the family. This can include adaptations to family life, the emotional impact, and the impact on relationships (child, siblings, peers, school, family, how they feel about themselves, and development of autonomy). The interview schedule may be an iterative process to ensure the situation involves IU and is appropriate for CUES in that it is current and presents an ongoing rather than a ‘one-off’ situation.This assessment protocol is based on that used by The Research Unit on Paediatric Psychopharmacology and Psychosocial Interventions [40] and has been used in previous anxiety and other treatment trials (e.g. [41, 42]). The IU target situations will be rated on a nine-point scale of improvement/deterioration independently by a panel of experienced clinicians. The top 3 points will define ‘a responder’. Arnold et al. [40] report ICC of 0.895 for a panel of five experts.

#### Secondary research outcomes

IU will be measured with the Intolerance of Uncertainty Scale (IUS-P and IUS-C; [43]) (parent reporting on child and (where possible) child self-report). Both are 12-item questionnaires. Both child (C) and parent (P) measures show acceptable to excellent internal consistency in ASD (α = 0.78 and 0.90, respectively) and typically developing groups (α = 0.76 and 0.91, respectively). We will also use the Intolerance of Uncertainty Scale (IUS-12; [7]) (parent self-report). This is a 12-item questionnaire, which has excellent internal consistency in a clinical sample (α = 0.91) and community sample (α = 0.92). The average inter-item correlation was 0.48 [7].Anxiety will be measured by three items. The Screen for Child Anxiety Related Disorders (SCARED; [44]) (parent reporting on child) is a 41-item questionnaire which has demonstrated good internal consistency (α = 0.74–0.93), test-retest reliability (ICC 0.70–0.90), and discriminative validity, both between anxiety and other disorders and within anxiety disorders [44]. The Anxiety Scale for Children — ASD – Parent and Child versions (ASC-ASD; [31]) (parent reporting on child and (where possible) child self-report) both (parent and child versions) have 24 items, and have demonstrated good to excellent internal consistency (α = 0.85–0.91), validity with measures (including sensory processing hypersensitivity, repetitive behaviours, depression, and anxiety), and 1 month test–retest reliability (*r* = 0.84, ICC = 0.84 for parent; *r* = 0.82, ICC = 0.82 for child) [31]. The Depression, Anxiety and Stress Scale (DASS; [45]) (parent self-report) is a 42-item questionnaire. This has acceptable reliability (α = 0.84–0.91), and convergent and discriminant validity [45].Participation and enjoyment will be assessed with the Children’s Assessment of Participation and Enjoyment (CAPE; [46]) (child self-report). This is a 55-item questionnaire, which has demonstrated good internal consistency (α = 0.30–0.62, which is expected due to the environmental, family, and child factors that affect participation), test–retest reliability (ICC = 0.64–0.86), and sufficient content and construct validity [46].Self-efficacy will be assessed with the Parent self-efficacy [47] (parent self-report). This is a 15-item questionnaire that ask parents to rate their confidence and self-efficacy in relation to behaviours targeted in clinical studies (in this case anxiety and IU-related behaviours). It is widely used for parent-mediated interventions and there are reliability and validity data available.Reactions to uncertainty and confidence will be measured using a bespoke questionnaire administered to parents each week of the CUES programme (parent reporting on self and child).Resource use will be assessed with a bespoke questionnaire given to parents measuring health resource use associated with IU in their child.Time and travel costs will be assessed with a bespoke questionnaire administered to parents measuring the travel costs and travel time associated with managing their child’s IU.

### Data collection and data management

Figure 2 details the information collected at different time points. To reduce burden for the family, follow-up assessments using questionnaire measures will be completed by post and the IU scenarios outcome measure will be rated by parents during follow-up telephone semistructured interviews with the blinded researcher. Northumberland Tyne and Wear NHS Foundation Trust may audit the data collected. Data collected on paper assessment tools will be entered onto a secure statistical analysis software system. A unique trial number will be used to identify participants on all paper data collection forms throughout the duration of the trial. No participant-identifiable data will leave the study site. The quality and retention of study data will be the responsibility of the principal investigator. All study data will be retained in accordance with the latest Directive on Good Clinical Practice (2005/28/EC) and local policy. Staff involved in the conduct of the trial, including the principal investigator, Trial Management Group and therapist staff involved in screening and intervention, will have access to the site files. Clinical information shall not be released without the written permission of the participant, except as necessary for monitoring and auditing by the Sponsor, its designee, regulatory authorities, or the REC. The principal investigator and staff involved in this trial may not disclose or use for any purpose, other than performance of the trial, any data, record, or other unpublished, confidential information disclosed to those individuals for the purpose of the trial.

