**Method:**

This is a feasibility and acceptability single-blind pilot randomised controlled trial comparing CUES (intervention) to a brief psychoeducation, emotional literacy, and relaxation programme (enhanced services as usual). Participants will be assessed at baseline and followed-up immediately post-treatment, and at 12 and 26 weeks post-treatment. Parents who have a child with ASD and anxiety (aged 6–16 years) will be invited to take part in the study and written parental informed consent and child assent will be obtained. Participants will be recruited from the National Health Service mental health teams in the UK. Sixty participants will be randomised to either intervention or enhanced services as usual in a 1:1 ratio.

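### The protocol names both a clinician panel and the unblinded parents as raters of the main research outcome, so the single-blind claim is not secured for it

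*Protocol article*

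**What the plan says.** The Method part of the abstract describes the design: "This is a feasibility and acceptability single-blind pilot randomised controlled trial". Four statements elsewhere in the protocol article bear on who rates the main research outcome and who is blind.

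- **Parents.** Randomisation and blinding: "Participants will be aware of group status due to the nature of the intervention".
- **Assessor.** The same section states that "the primary outcome assessor will be blind to group allocation", without identifying that person. It adds that, although told not to, "participants could unwittingly break blindness if they reveal details about the intervention at post-treatment assessment".
- **Panel.** Main research outcome introduces the measure as parent-reported: "The main research outcome is to target uncertain situations that cause the child to experience anxiety due to IU (parent reporting on child"). It then says: "The IU target situations will be rated on a nine-point scale of improvement/deterioration independently by a panel of experienced clinicians". On responder status it continues "The top 3 points will define" a responder.
- **Parent rating.** Data collection and data management: "the IU scenarios outcome measure will be rated by parents during follow-up telephone semistructured interviews with the blinded researcher".

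**The concern.** The outcome is a judgement of how far a child's difficulty with chosen real-life situations has changed. Such a judgement depends heavily on who makes it and what that person knows. If the parent gives the score, the score is unblinded whatever the interviewer knows.

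The two arms also differ in how closely they touch the thing being rated. CUES parents practise programme strategies on a target situation. Control sessions are meant to avoid anxiety and intolerance of uncertainty altogether. Expectation could therefore act unequally, and a CUES parent describing the situation may find it hard not to reveal the arm.

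At stake is the use made of the results. Aim 8 compares the arms on reduction in real-life intolerance of uncertainty and anxiety. Aim 10 follows any effects to 6 months. The Discussion says that the data will inform the design and sample size of a full-scale trial. A responder rate or mean change whose rater is unclear is a weak basis for that.

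**Working it through.** The plan states no figure on this point, so there is nothing to reproduce. The check sets the sections side by side.

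**Step 1: is it the same measure?** Main research outcome speaks of target situations and Data collection and data management of scenarios. Both concern intolerance of uncertainty, and both describe information obtained from parents by semistructured interview. No other outcome in the article fits the second description, so I read them as one measure.

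**Step 2: who gives the score, and is that person blind?**

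| Section | Who rates | Blinding stated for that rater |
|---|---|---|
| Main research outcome | Clinician panel, nine-point scale | None; rating is said to be independent |
| Data collection and data management | Parents, by telephone | None; only the interviewing researcher is called blinded |
| Randomisation and blinding | An unidentified assessor | Blind; parents are expressly not blind |

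**Step 3: do the statements fit together?**

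- *Parent score governs.* The rater knows the allocation. The interviewer's blinding protects how questions are put and recorded, not the score itself.
- *Panel score governs.* Rating independently means that each member rates without the others. It does not mean that members are masked to arm. The article does not say what material they see, whether mentions of the arm are removed, or whether the panel is the blinded assessor.
- *Both scores exist.* No section says how they relate or which one is analysed.

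**Step 4: could the bias differ between arms?** Contact time from the Treatment section:

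- CUES: 8 sessions × 2 h = 16 h, with a chosen target situation as the focus for practice.
- Understanding Autism: 2 sessions × 2 h = 4 h, on other topics.

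This makes a bias towards CUES the more likely direction. It does not give its size. The article states no responder rate, standard deviation or expected effect, so any figure for the bias would be an assumption with no anchor in the documents.

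**The case against.** The strongest reply is that the sections describe two stages of one procedure. The outcome is labelled as parent-reported, a blinded researcher takes the parent's account by telephone, and the panel then rates change. On that reading, the sentence under Data collection and data management is loose wording, and interviewer and panel may both be blind. The reading is plausible, but the text does not state it: it says that parents rate. So the need to reconcile the sections stands.

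Several stronger inferences are tempting, and the documents do not support them.

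- *The analysed outcome is unblinded.* That follows under one reading only.
- *Nothing protects the blind.* Parents are instructed not to reveal their arm, and the protocol openly admits the remaining risk. The safeguard is partial, but it exists.
- *People who know the allocation sit on the panel.* The principal investigator and the clinical lead supervise CUES and monitor its sessions by video. No section places either on the panel or says that they know each family's target situation. Panel membership is simply not described, and a condensed article may leave that to the full protocol.
- *The trial's main conclusions are compromised.* The principal aims are feasibility, acceptability and informing a full trial. Planned analyses calls the effect analyses preliminary, says that the study is not designed to test a treatment difference, and specifies differences in mean change rather than a responder contrast. It asks for cautious interpretation, though because of size and baseline imbalance, not blinding.

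These points limit the severity. They do not remove the contradiction, and reporting a biased estimate descriptively does not make it unbiased.

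**Conclusion.** The point holds as an unreconciled contradiction about who scores the main research outcome. The panel and the parents are both named as raters. The parents are unblinded, and the panel is not said to be masked. The single-blind description is thus not secured for this outcome, although it may turn out to be true in practice.

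The consequence is conditional. If the parent score is used, the preliminary effect and responder estimates may be biased, probably in favour of CUES, by an amount that the documents do not allow one to estimate. The conclusion assumes that the target situations and the scenarios are the same measure, and that no part of the plan outside this article settles the rater. The effect is confined to the estimates carried forward to the next trial. The change should be made, but the feasibility and acceptability aims do not depend on it.

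**What to change.** Reconcile Randomisation and blinding, Main research outcome, and Data collection and data management so that one pathway governs.

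1. The blinded researcher records the parent's description of each target situation. The panel's nine-point rating alone defines the outcome and responder status.
2. State that the panel is blind to allocation and rates written accounts from which mentions of arm, sessions and programme strategies have been removed.
3. State that panel members have not supervised or viewed sessions of either programme.
4. Replace the wording that has parents rate the measure, or keep a parent score as a separate secondary outcome labelled unblinded.
5. Record any unblinding of the interviewer or panel.
6. State that the accounts come from unblinded parents, so that masking the panel reduces bias but does not remove it.

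The cost is protocol wording and some redaction time before panel rating. The panel is already planned, but item 3 may limit who can serve on it, and membership is not given.

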**Fig. 2 Fig2:**
[figure not shown]
Time points at which measures and data are collected. ADIS-ASA Anxiety Disorders Interview Schedule — Autism Spectrum Addendum, ASC-ASD Anxiety Scale for Children — Autism Spectrum Disorder, CAPE Children’s Assessment of Participation and Enjoyment, CUES Coping with Uncertainty in Everyday Situations, DASS Depression, Anxiety and Stress Scale, IUS-C Intolerance of Uncertainty Scale Child, IUS-P Intolerance of Uncertainty Scale Parent, SCARED Screen for Child Anxiety Related Disorders, SCQ Social Communication Questionnaire, VABS III Vineland Adaptive Behaviour Scales III

### Planned analyses

Sydes and colleagues [48], who reviewed requirements for data monitoring committees (DMCs), concluded that DMCs are recommended when trials have any of the following features: trials on high-profile topics that are a focus of community concern, that will be used to seek regulatory approval or that are likely to profoundly affect clinical practice; trials with serious safety concerns, unknown risks or that are implemented in vulnerable populations; and trials where independent monitoring is needed because of double-blind treatment assignment or long-term follow-up or because the sponsoring company does not have standard operating procedures. DMCs may not be needed: 1) for trials that are of short duration (where it may not be feasible to convene a DMC in a timely fashion to review the data); 2) for trials with known risks that are minimal; 3) for trials in which the objective is to demonstrate principles (such as in early-phase clinical trials); or 4) for trials on behavioural or administrative issues. In the current case, given the acceptability and feasibility aims where we are constantly monitoring events that could relate to acceptability and feasibility such as nonattendance (for any reason) and, if not informed of a reason, this is followed-up, coupled with the short duration, minimal risks, and the parent-delivery of treatment, it was determined that a DMC was not required. In this case, data management will be discussed at Trial Steering Committee meetings.

As this is a feasibility study, analyses will be mainly descriptive, and no interim analysis will be undertaken. Formal power calculations are not appropriate as the study is not designed to test for a difference between treatments. Feasibility will be explored by examining: 1) the number of families who consented, their attendance, and complete data at 6 months; and 2) that qualitative data support the acceptability of CUES by the majority of parents and clinicians.

We will also undertake some preliminary analysis of treatment effects. As a randomised controlled trial, primary analysis will be based on the intention-to-treat principle with analysis based on groups allocated at randomisation and all randomised families included. The extent of missing data will be assessed. Rates will be calculated as defined and reported with 95% confidence intervals. At baseline and by group, the distribution of all variables will be examined and summarised by measures of central location and spread and reported with 95% confidence intervals. Baseline categorical variables will be tabulated and percentages reported with 95% confidence intervals. The difference in mean change for all outcome measures will be examined between the groups from baseline to each of the two time points with accompanying 95% confidence intervals. Evidence of clustering and/or contamination will be explored. Such results will be interpreted cautiously because of the size of the study and the possible imbalance in prerandomisation baseline covariates. The relationship between baseline covariates and outcome measures will be examined graphically and quantified appropriately depending on their distribution.

While no formal economic evaluation will be undertaken at this stage, questionnaires have been designed in conjunction with patient representatives which will measure resource use associated with managing IU. The data gathered from these questionnaires will provide information about healthcare resource use and personal costs to families which will aid the design of a potential future economic evaluation associated with a full trial. Numbers of families who express interest, continue to treatment, and who complete treatment will be recorded. When families do not participate/complete treatment, the reasons for this will be investigated, if appropriate and where possible, through brief telephone interviews or visits to families. The study team and the health economist will advise on the content of the interview schedule.

When appropriate, interviews will be recorded, transcribed, double-coded, and analysed using thematic analysis [49].

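### Preliminary treatment effects on the questionnaires are estimated from unadjusted change scores, although adjusting for the collected baseline score would be more precise and would deal with chance baseline imbalance

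*Protocol article*

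**What the plan says.** Planned analyses in the protocol article describes the effect estimate in one sentence: "The difference in mean change for all outcome measures will be examined between the groups", measured from baseline to two follow-up times, with 95% confidence intervals. No covariate, and in particular no baseline value of the outcome, is said to enter that comparison.

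The same section says that the results will be "interpreted cautiously because of the size of the study and the possible imbalance in prerandomisation baseline covariates". It then adds: "The relationship between baseline covariates and outcome measures will be examined graphically and quantified appropriately depending on their distribution". That step is not linked to the comparison between arms. The analysis set is by intention to treat, with "analysis based on groups allocated at randomisation and all randomised families included"; on missing data, the section says only that its extent will be assessed.

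Randomisation and blinding states 1:1 allocation "without stratification", and the Abstract gives 60 participants, so about 30 per arm. Planned analyses also says that the analyses are mainly descriptive and that the study is not designed to test for a treatment difference.

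**The concern.** The article chooses an estimator here; it does not simply leave one to a later document. It collects baseline questionnaire scores, allocates without stratification in a small sample, and names baseline imbalance as a possibility. It then picks a comparison that uses the baseline score inefficiently. Subtracting the baseline amounts to fixing its regression coefficient at 1, whereas the best coefficient, with equal SDs, is the baseline/follow-up correlation. Whenever that correlation is below 1, the subtraction takes away too much. Noise is added, and a chance difference at baseline reappears in the estimate with its sign reversed.

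Aims 8 and 10 ask whether children in the CUES arm improve more and whether any effect persists at 6 months, and the Discussion says the data will inform the design and sample size of a full-scale trial. Avoidable noise and an avoidable conditional shift would carry into those decisions.

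**Working it through.** **Inputs from the article.** 60 families at 1:1, so n = 30 per arm; no stratification; 95% intervals, taken as two-sided. The article states no SD, effect size or power, so there is no figure of its own to reproduce.

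**Assumptions.** Equal SDs at baseline and follow-up (set to 1), and a baseline/follow-up correlation ρ, which the article does not give. Secondary research outcomes reports 1-month test–retest values of 0.84 (parent) and 0.82 (child) for the ASC-ASD. These serve as an upper guide, because the last follow-up is 26 weeks after treatment. The range shown is 0.3 to 0.84.

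**Precision.** Per-family variance for each estimator:
- change score: 2(1 − ρ)
- baseline-adjusted (ANCOVA): 1 − ρ²
- ratio: (1 − ρ²) / [2(1 − ρ)] = (1 + ρ)/2

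The 95% half-width for the change score is t × √(variance × 2/30) on 58 degrees of freedom. For ANCOVA it uses 57 degrees of freedom and a factor √(1 + 1/56) for estimating the slope.

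**Conditional shift.** If the arms differ by D on the outcome's own baseline, the expected follow-up difference contains ρD. Subtracting D leaves (ρ − 1)D in the change-score estimate. ANCOVA subtracts ρD and leaves nothing. The last column takes D = +0.3 SD.

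| ρ | 2(1 − ρ) | 1 − ρ² | Ratio | Half-width, change (SD) | Half-width, ANCOVA (SD) | Shift of change score (SD) |
|---|---|---|---|---|---|---|
| 0.3 | 1.40 | 0.91 | 0.65 | 0.61 | 0.50 | −0.21 |
| 0.5 | 1.00 | 0.75 | 0.75 | 0.52 | 0.45 | −0.15 |
| 0.7 | 0.60 | 0.51 | 0.85 | 0.40 | 0.37 | −0.09 |
| 0.84 | 0.32 | 0.29 | 0.92 | 0.29 | 0.28 | −0.05 |

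In large-sample terms, adjusting 60 families is worth 60/0.75 = 80 families analysed by change score at ρ = 0.5, 60/0.85 ≈ 71 at 0.7, and 60/0.92 ≈ 65 at 0.84.

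**Small-sample check.** In 20,000 simulated trials with 30 per arm, the variance ratio was 0.776 at ρ = 0.5 and 0.938 at ρ = 0.84. The gains are therefore about 22% and 6%, against 25% and 8% from the formula.

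**How likely such an imbalance is.** The SD of a chance baseline difference is √(2/30) = 0.258. Then P(|D| > 0.3) = P(|Z| > 0.3/0.258) ≈ 0.245, about one in four for any one outcome.

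**The case against.** The strongest reply is that little depends on this estimator. The study is a feasibility trial, its effect analysis is labelled preliminary, the limitation is disclosed, and no feasibility criterion uses the estimate. If correlations are as high as the ASC-ASD test–retest values, the interval barely moves (0.29 to 0.28 SD). All of this stands. It limits the weight of the point but does not remove it, since lower correlations over a longer interval are plausible and the remedy is nearly free.

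Some stronger readings are tempting but not supported:

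- **That the estimator is biased.** It is unbiased over randomisations. The shifts above are conditional on a given imbalance.
- **That the plan expects imbalance.** It speaks only of "the possible imbalance in prerandomisation baseline covariates".
- **That imbalance is left uncorrected.** For the outcome's own baseline, the change score corrects too much. For other covariates, no correction is stated.
- **That families are dropped, contrary to "all randomised families included".** A raw change score does need both values, so that statement requires some missing-data method. But the article sets no complete-case rule, and the method may be in a statistical analysis plan that is not shown. Its silence is not a completer analysis.
- **That the main research outcome is affected.** That outcome is a clinician panel's rating of improvement or deterioration with a responder definition. It has no baseline value of its own, so the argument is confined to the questionnaires.

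**Conclusion.** The point holds for the questionnaire outcomes. The stated unadjusted change-score difference is valid but less efficient than a baseline-adjusted one, and cautious interpretation does not remove the over-correction that follows a chance baseline imbalance. The size depends on ρ: a variance reduction of about 25% at 0.5, 15% at 0.7 and 8% at 0.84, a few points less with 30 per arm. For a 0.3 SD imbalance, the avoidable shifts are about 0.15, 0.09 and 0.05 SD. These figures rest on equal SDs, a linear baseline/follow-up relation and an assumed correlation. The change is worth making because the estimates are meant to inform a full trial; it is not a flaw that undermines the feasibility aims.

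**What to change.** In Planned analyses, state that for each questionnaire outcome with a baseline score (IUS-P and IUS-C, IUS-12, SCARED, ASC-ASD, DASS, CAPE, parent self-efficacy) the arm difference at each follow-up will be estimated with adjustment for that outcome's baseline value and reported with a 95% confidence interval. Keep raw mean change by arm as a descriptive table.

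ANCOVA at each follow-up already delivers the precision gain. A longitudinal mixed model over the follow-ups is an alternative. The two ways of handling baseline in that model are not interchangeable: with baseline as a covariate, a family with no follow-up score still falls out, whereas with baseline in the response vector and arm means constrained equal at baseline, such a family stays in the model. Leave the panel-rated main outcome on its own scale.

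The cost is a few sentences of analysis wording. No extra data, visits or families are needed.
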